### Participants information and outcome of measures

2.4

Using surveys administered by trained enumerators, information about participants’ socio-demographics and the outcomes of measures includes knowledge of nutrition, dietary habits, food security, anthropometrics and biomarker indicators will be obtained at baseline and post-intervention. Acceptability of the intervention will be included in the post-intervention survey. Information about their engagement, and knowledge retention intervention will be tracked during the WhatsApp nutrition education delivery. Table 2 describes the study activities in details.

The validity and reliability of the tools used to measure study outcomes is described below. All adapted and newly developed tools described below will be assessed for internal consistency by calculating Cronbach’s Alpha to determine the correlation between items measuring each construct.

#### Primary outcomes

2.4.1

##### Awareness and interest in indigenous vegetables and fruits

2.4.1.1

Given the novelty of this outcome, we developed a six-item questions that cover questions about participant’s awareness of IVFs, interest in IVF gardening, nutritional benefits, barriers to consumption, and their role in enhancing health and well-being were developed with input from agricultural experts for content validity. This measure will assess improvement in awareness and knowledge of IVFs resulting from their participation.

##### Household food security

2.4.1.2

The study population’s household food security will be measured by using Household Food Insecurity Access Scale (HFIAS). This tool was developed by the Food and Nutrition Technical Assistance Program of the US Agency for International Development has demonstrated validity and reliability in low- and middle-income countries (46). The HFIAS consists of nine occurrence questions targeted at the food access experience of the participants. Each question has 3 responses, namely, rarely (once in the past 4 weeks), sometimes (three to ten times in the past 4 weeks), and often (more than ten times in the past 4 weeks), with scores of 1, 2, and 3, respectively. The scores will be summed to a maximum of 27. The HFIAS will be considered as a continuous variable with higher scores indicating greater susceptibility to food insecurity (46).

##### Nutritional knowledge and practices

2.4.1.3

A four-item question, one about their knowledge of five-a-day recommendation and three about participants’ nutritional knowledge and practices on IVF will assess the change in nutritional knowledge and practices between pre- and post-intervention. These nutrition practice questions were adapted from the validated food behavior checklist (47).

##### Indigenous vegetables and fruits specific self-efficacy

2.4.1.4

A five-item question will assess the participants’ confidence in the selection, preparation, and consumption of IVFs. These questions were adapted from a previously validated 24-item self-efficacy consumption of fruit and vegetable (48), and food safety psychosocial questionnaire (49) to capture changes in self-efficacy related to the choice, preparation, and consumption of IVFs.

##### Food safety self-efficacy and practices

2.4.1.5

A six-item question on food safety self-efficacy was adapted from the food safety self-efficacy construct of a previously food safety psychosocial questionnaire that had demonstrated validity and internal consistency (49). The set of questions will measure the participants’ confidence in practicing safe methods of handling, storing, and preparing food. A descriptive statistics test will be used to determine the participants’ self-efficacy practice levels of food safety at the pre-and post-intervention.

##### Household dietary diversity

2.4.1.6

The household dietary diversity score (DDS) is a validated proxy measure that reflects a household’s economic ability to access a variety of foods (50). It has demonstrated good content and construct validity, and has been applied reliably across multiple cultural and socioeconomic contexts. It assessed household food access using a structured scoring system based on the consumption of various food groups by participants (51). The assessment shall be made on the food categories of cereals and grains: bread, rice, noodles, biscuits, millet, maize, etc., roots and tubers; eggs; fish and shellfish; legumes and nuts; dairy products, such as milk, cheese, yogurt; fats and oils; sugars and honey; and miscellaneous foods, including condiments, coffee, and tea. Scores shall be given as 1 point for every category taken and 0 for those not taken. In measuring the cumulative DDS, the food items across all food groups will be summed; hence, the maximum score possible will be 12. The higher the dietary diversity score, the higher the dietary diversity. A descriptive statistic of the dietary diversity of the participants, using the score threshold of 0–4 for low dietary diversity, 5–8 for medium dietary diversity, and 9–12 for high dietary diversity scores will be used (10).

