Specifically, the study will assess the impact of a school-based gardening program and WhatsApp-based nutrition education interventions on primary outcomes such as youths’ nutrition knowledge, fruit and vegetable-specific self-efficacy, food security, dietary diversity, anthropometric data, and skin carotenoid level. In this study, school-based gardening refers to structured gardening activities conducted within a school setting involving in-school and out-of-school youths residing in the same community as the school. These activities will engage participants in cultivating and harvesting vegetables to enhance agricultural skills, nutrition awareness, and healthy eating habits. This intervention will be guided by the Cognitive Theory of Multimedia Learning (CTML), Social Cognitive Theory (SCT), and Empowerment Theory (ET), all of which are described in details in the method section below. Furthermore, the study will also examine secondary outcomes such as the participants’ engagement, knowledge retention, and acceptability of the intervention.

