**Null Hypothesis:**
*There is no difference in nutrition knowledge, fruit and vegetable self-efficacy, dietary habits, and biochemical data between youth who receive the combination of school-based gardening of IVFs, and WhatsApp nutrition education compared to those who receive only school-based gardening of indigenous fruits and vegetables.*

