**Alternative Hypothesis:**
*There is a significant difference in nutrition knowledge, fruit and vegetable self-efficacy, dietary habits, and biochemical data between youth who receive the combination of school-based gardening of IVFs and WhatsApp nutrition education compared to those who receive only school-based gardening of indigenous fruits and vegetables.*

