Technical guide support for the gardening activities			√	
Multimedia messaging for WhatsApp education intervention group			√	
Tracking WhatsApp education participants’ engagement and knowledge retention			√	
Participants’ socio-demographic characteristics		√		√
Participants’ awareness and interest in indigenous vegetables and fruits		√		√
Participants’ household food security		√		√
Participants’ nutrition knowledge and practices		√		√
Participants’ fruits and vegetables specific self-efficacy		√		√
Participants’ food safety self-efficacy and practices		√		√
Participants’ dietary diversity		√		√
Participants’ anthropometric measures and biomarker data collection		√		√

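### Section 2.4.1.6 gives one primary outcome two units, household food access and the participant's own intake, so the meaning of the arm effect on dietary diversity is not settled

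*Protocol article*

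**What the plan says.** Section 2.4.1.6 is headed as a household measure and presents the score as a validated proxy for "a household’s economic ability to access a variety of foods". Shortly afterwards one sentence holds both units: "It assessed household food access using a structured scoring system based on the consumption of various food groups by participants". The section ends by planning a descriptive summary of the participants' diversity in bands of 0–4, 5–8 and 9–12, out of a stated maximum of 12.

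Elsewhere in the protocol article:

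- Table 2 lists the outcome as "Participants’ dietary diversity".
- The Introduction places it among the primary outcomes: "youths’ nutrition knowledge, fruit and vegetable-specific self-efficacy, food security, dietary diversity, anthropometric data, and skin carotenoid level".
- The null hypothesis concerns "dietary habits, and biochemical data between youth who receive the combination" and those who only garden. The alternative is framed the same way.
- Section 2.2 says that everyone gardens and that half (130) also receive the WhatsApp course.
- Section 2.5 names the diet diversity score as one of three outcomes for the mixed model, with skin carotenoids and anthropometrics. Arm, time and their interaction are in the model, and household size is a covariate.

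No section says whether respondents report what they ate themselves or what anyone in the household ate.

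**The concern.** A household score asks whether any member ate a food group, as a marker of what the household can obtain. An individual score asks whether the youth ate it. They answer different questions and can move separately: a youth who starts eating a food that others at home already eat changes the second score but not the first.

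The difference matters in this design because both arms get the garden, plots, seeds and equipment. Any gain in household food access from gardening is open to both arms. The contrast in the mixed model isolates a course taken by individual youths. On the household reading, the model estimates the course's effect on household access. On the participant reading, it estimates the effect on the youth's diet, which is what the hypotheses address. As written, a reader of the results could not tell which had been estimated.

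**Working it through.** **Planned size, for context.** Section 2.2.1 gives z = 1.96, proportion 0.188 and margin 0.05. So n = 1.96² × 0.188 × 0.812 / 0.05² = 234.6, rounded up to 235, as stated. Allowing for 10% dropout gives 235/0.9 ≈ 262 or 235 × 1.1 ≈ 259, consistent with the stated 260 or so. This figure rests on an unemployment proportion and says nothing about the dietary diversity score. It is used here only for the number of completers: 130 × 0.9 = 117 per arm.

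**Which unit each place implies.**

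- Household: the heading of 2.4.1.6, its definition, and the validation it cites.
- Participant: the scoring clause in 2.4.1.6, its closing sentence on reporting, and the hypotheses if dietary habits include this score.
- Open to either reading: Table 2 and the list in the Introduction (see the objection).

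The conflict is already complete inside 2.4.1.6.

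**What the household reading could do to the arm effect.** The article gives no household size, no base rate and no effect size, so what follows is an illustration. Assume a household of h people, each eating a given food group independently with probability q, and assume that only the participant changes. The household item is scored 1 if anyone ate it. Raising the participant's own probability by Δ raises the household item by Δ × (1 − q)^(h−1).

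With h = 5, q = 0.3 and the participant going from 0.3 to 0.5:

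- before: 1 − 0.7⁵ = 0.832
- after: 1 − 0.5 × 0.7⁴ = 0.880
- household change 4.8 points against 20 points for own intake, a retained fraction of 0.7⁴ = 0.24

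For the same 20-point change, with q from 0.2 to 0.4 and h from 4 to 6, the household change runs from 20 × 0.6⁵ = 1.6 to 20 × 0.8³ = 10.2 points. With h from 2 to 6 and q from 0.1 to 0.5, the retained fraction (1 − q)^(h−1) runs from 0.90 down to 0.03.

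Independence drives these results. If the household eats from a common pot, the household item and the participant's item move together and the retained fraction is 1. It is also 1 if enumerators already score the participant's own intake.

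**What that would mean for power.** Assume a simple two-arm comparison of means, two-sided alpha 0.05, 117 per arm, the same SD on both scores, and no allowance for clustering or baseline adjustment. The standardized difference detectable with 80% power is (1.960 + 0.842) × √(2/117) = 0.366. If only a fraction f of it passes through:

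| f | Power | n per arm to restore 80% |
|---|---|---|
| 1 | 80% | 117 |
| 0.75 | 56% | 208 |
| 0.5 | 29% | 468 |
| 0.25 | 10% | 1872 |

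**The food-group list.** As printed, 2.4.1.6 names nine categories: cereals and grains; roots and tubers; eggs; fish and shellfish; legumes and nuts; dairy; fats and oils; sugars and honey; miscellaneous. At one point each the maximum is 9, not 12, and neither vegetables nor fruits appear. This bears on the fix, because asking the printed list about the participant would not register the foods the trial promotes.

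**The case against.** The best defence is that this is a household outcome, loosely described. The heading, instrument, definition and validation are all household. Table 2 uses the same possessive for food security while also calling it household, so the possessive need not mean individual intake. The Introduction's list includes food security too, which 2.4.1.2 measures at household level. No section ties the hypotheses' dietary habits to this score, and nutrition practices and skin carotenoids already cover the individual. Household access is a legitimate target. Nor is the course sealed off from the home: its tasks include cooking at home in week 2, sharing family recipes in week 5 and carrying out a meal plan in week 8. Question wording and enumerator instructions are commonly left out of an article.

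Much of this stands. A household measure is not in itself the wrong choice, and the home-based tasks are a plausible route to household change. Table 2 is weak evidence, though it can also be read the other way, since that table names the household for food security and not here. What does not stand is the idea that only detail is missing: the printed text states both units in a single sentence. If household access is meant, the score sits beside the HFIAS as a second household-access outcome, and it should not be reported as the participants' diversity.

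A reader might infer from the illustration that the arm effect is heavily diluted, or that a change in the youth's diet would be largely invisible. The protocol article does not support that. Household size, base rates and independent eating are all assumed, and dilution disappears under shared meals or own-intake scoring.

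**Conclusion.** The point holds as an unresolved unit for a primary outcome. Section 2.4.1.6 states a household-access score and a participant-intake score as one measure, and the choice decides what the arm effect in 2.5 means. If the household unit is used, the score does not directly measure the youth's own diet, and the effect of an individual course could be attenuated. The size cannot be fixed from the protocol article: the retained fraction runs from 1 (shared meals, or own intake scored) to 0.03 at the extreme of the assumed range, with 0.24 in the five-person example. Those figures show only that the unit can matter. They do not estimate a loss in this trial, and no finding that the outcome is wrong or heavily diluted follows from them.

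**What to change.** Before baseline collection, set one unit and use it in 2.4.1.6, Table 2 and 2.5.

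- Because the hypotheses concern youths, score the participant's own intake over a stated, fixed recall period, and use that score in the mixed model.
- Use a complete food-group list that matches the 12-point maximum and includes vegetables and fruits. The nine categories now printed should not simply be reused.
- If the household score is kept, label and interpret it as a food-access outcome alongside the HFIAS, not as the youth's dietary diversity.

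The cost is the rewording of one question block and the matching labels. The real downside is that the household score's validation and its low, medium and high cut-offs would not carry over directly to an individual score. Timing matters because answers given for the household cannot later be turned into the participant's own intake.

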### Data analysis

2.5

Descriptive statistics such as frequency and percentages will be used for the socio-demographic characteristics (such as age, gender, student status, and household size) and other outcome of measures (such as knowledge retention, intervention acceptability, and nutrition-related outcomes) that are categorical variables, while mean and standard deviation will be used for the continuous variables. To assess the possibility of bias resulting from missing data, we will conduct sensitivity analyses by carrying out complete case analyses. As opined by Braun and Clarke, this will ensure the robustness and credibility of our result (61). Mixed model analyses will be used to assess the intervention’s impact on skin carotenoid levels, anthropometrics, and diet diversity score (62, 63). The mixed model analysis was chosen because it accounts for repeated measures and can effectively address issues related to missing data. In these analyses, the intervention arms will be treated as the fixed effect so that the measure’s outcome change between the school gardening-only participants and school gardening and nutrition education participants can be assessed by the coefficients or estimated using the least square means. Time and intervention arm will be included as both main effects and interaction effects. The random effect will account for variability variations between groups that might affect the response. We will control for participant’s age, gender, household size, youth status (out-of-school vs. in-school status), community, and state, by including them as covariates in the adjusted models of the mixed model analysis. Mann–Whitney U Test will be used to compare the acceptability of the nutrition intervention between the groups. The analysis will be performed using IBM SPSS (version 23), and the statistical significance will be set at *p*-value <0.05.

As described by Braun and Clarke (61), the participants’ audio (sessions responses) and video recordings (tasks) from WhatsApp engagement will be analyzed using thematic analysis. We will use inductive coding to deduce the theme directly from the data. The convergent mixed method will be used to integrate the qualitative analysis with the quantitative results. This ensures a proper understanding of how participants experienced and engaged with the intervention.

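### The dietary diversity score lists nine food groups against a stated maximum of 12, and the list names neither vegetables nor fruits

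*Protocol article*

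**What the plan says.** Section 2.4.1.6 (Household dietary diversity) of the protocol article fixes the score in four steps.

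- The categories: "The assessment shall be made on the food categories of cereals and grains: bread, rice, noodles, biscuits, millet, maize, etc., roots and tubers", followed by "eggs; fish and shellfish; legumes and nuts; dairy products, such as milk, cheese, yogurt; fats and oils; sugars and honey; and miscellaneous foods". Condiments, coffee and tea are given as examples of the last category.
- The scoring rule: "Scores shall be given as 1 point for every category taken and 0 for those not taken".
- The total: "In measuring the cumulative DDS, the food items across all food groups will be summed; hence, the maximum score possible will be 12".
- The bands, for a descriptive summary: "0–4 for low dietary diversity, 5–8 for medium dietary diversity, and 9–12 for high dietary diversity scores".

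The score is a primary outcome. Section 2.4.1 includes it, and the Introduction names "food security, dietary diversity, anthropometric data, and skin carotenoid level" among the primary outcomes. Section 2.5 (Data analysis) uses a mixed model with time, arm and their interaction to assess the "impact on skin carotenoid levels, anthropometrics, and diet diversity score".

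**The concern.** The list, the scoring rule and the stated maximum cannot all be right. With one point per category, the maximum equals the number of categories, and the list is shorter than 12.

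The content of the gap matters more than the count. Participants in both arms grow indigenous vegetables and fruits, and the WhatsApp curriculum teaches their value and use. No listed category covers either food. If the survey form follows the text, a household that starts eating both gains nothing directly on this outcome. A real dietary change could then go unseen in the between-arm comparison of this score. Food groups not asked about at baseline cannot be recovered reliably later.

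This goes beyond the shortening expected of a journal article. The section presents the list as the set of categories to be assessed, gives examples inside several of them, and does not refer to a fuller list. No other section supplies the missing groups.

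**Working it through.** **Inputs**, all from section 2.4.1.6: the category list, one point per category taken, a maximum of 12, and bands of 0–4, 5–8 and 9–12.

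**Count of categories**

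1. Cereals/grains
2. Roots/tubers
3. Eggs
4. Fish/shellfish
5. Legumes/nuts
6. Dairy
7. Fats/oils
8. Sugars/honey
9. Miscellaneous

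**Attempt to reproduce the stated maximum.** Maximum = number of categories × 1 point.

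| Reading of the list | Categories | Maximum | Short of 12 by |
|---|---|---|---|
| Roots/tubers counted as its own group | 9 | 9 × 1 = 9 | 12 − 9 = 3 |
| Split only at semicolons, so roots/tubers joins cereals | 8 | 8 × 1 = 8 | 12 − 8 = 4 |

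Neither reading gives 12. The first is the natural one, because the foods given as examples before roots and tubers are mostly cereal products.

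**Effect on the bands.** With nine categories the range is 0–9. Scores of 10, 11 and 12 cannot occur, and the high band shrinks to the single value 9, reached only by taking all nine groups. With eight categories the high band could not be reached at all.

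**Effect of eating more vegetables and fruits.** Neither food is a listed category, so the direct gain is 0 + 0 = 0 points. If each were a separate group, a household newly taking both would gain 1 + 1 = 2 points.

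**Does adding them restore 12?** 9 + 2 = 11, which leaves 12 − 11 = 1 group that the article does not name.

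**The summing sentence.** It speaks of adding food items, whereas the sentence before it gives one point per category. A sum of items would not be capped by the number of groups. Since the same sentence concludes "hence, the maximum score possible will be 12", adding category points is probably meant. The wording is loose and needs tidying, but it is not a second firm contradiction.

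**The case against.** The strongest reply is that the list was copied incompletely from a validated 12-group tool. The stated maximum and all three bands point that way, and the survey form is not shown. On that view the form may already ask about vegetables and fruits, and only the article is wrong. As a reading of intent this is plausible, and it limits what can be claimed. It does not remove the defect, because the article's operative definition contradicts its own maximum and enumerators and analysts need a single definition.

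Several stronger readings are tempting, but the documents do not support them.

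- **That the outcome cannot respond to the intervention at all.** Only the direct route is closed. The curriculum also covers a balanced plate (week 1) and meal planning (week 8), so other groups could change and move the score.
- **That the trial cannot detect a change in fruit and vegetable intake.** Section 2.4.1.7 assesses that intake separately with skin carotenoids, which also enter the mixed model. The abstract lists fruit and vegetable intake apart from dietary diversity, and section 2.4.1.6 presents the score as a proxy for household access to varied food.
- **That this is one of only three outcomes compared between arms.** It is one of three measures named for the mixed model. Section 2.5 also compares acceptability between the groups with a Mann–Whitney test.
- **That the bands themselves are wrong.** If the list is the error, the bands can stand. They also serve only a descriptive summary, while the model is said to use the score.
- **That the twelfth group can be named from here.** No section identifies it, so it has to come from the cited instrument.

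**Conclusion.** The point holds as a scoring definition that is wrong as written for one primary outcome. The listed categories allow a maximum of 9 (8 on the narrower reading) against a stated 12. Vegetables and fruits earn no points directly.

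The count rests on the text alone. The consequence for the trial depends on one assumption, that the survey form and the scoring follow section 2.4.1.6 as printed. If they do, this score gives no direct credit for the foods the intervention promotes, and the high band means taking every listed group. If the form already carries 12 groups including vegetables and fruits, the data are unharmed and only the text needs correcting. Either way the defect is confined to dietary diversity.

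The size of any lost treatment effect cannot be given, because the article reports no figures on how many households would newly take vegetables or fruits.

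**What to change.** Before baseline data are collected:

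1. List every scored food group in section 2.4.1.6, with vegetables and fruits as explicit, separate groups. This gives 11.
2. Confirm the remaining group against the cited instrument so that the list, the maximum of 12 and the bands agree. Otherwise, restate the maximum and the bands to fit the list actually used.
3. Check that the survey form carries the same groups.
4. Reword the summing sentence to say that category points will be summed.

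The cost is a wording correction and, if the form follows the present text, a few yes/no items. No extra participants or visits are needed.

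### The dietary diversity score is said to sum food items where its own rule gives one point per category, and the nine printed categories do not reach the stated maximum of 12

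*Protocol article*

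**What the plan says.** Section 2.4.1.6 (Household dietary diversity) describes the score as a "structured scoring system based on the consumption of various food groups by participants". It then lists the categories: "cereals and grains: bread, rice, noodles, biscuits, millet, maize, etc., roots and tubers; eggs; fish and shellfish; legumes and nuts", followed by "dairy products, such as milk, cheese, yogurt; fats and oils; sugars and honey; and miscellaneous foods, including condiments, coffee, and tea".

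The scoring rule is "Scores shall be given as 1 point for every category taken and 0 for those not taken". The next sentence defines the total: "In measuring the cumulative DDS, the food items across all food groups will be summed; hence, the maximum score possible will be 12". The score is then to be described in bands: "0–4 for low dietary diversity, 5–8 for medium dietary diversity, and 9–12 for high dietary diversity scores".

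The outcome stands under section 2.4.1, "Primary outcomes". Section 2.5 (Data analysis) names it among the outcomes for the mixed model: "skin carotenoid levels, anthropometrics, and diet diversity score".

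**The concern.** The sentence that defines the total names food items as the thing summed, and mentions food groups only as what the items are summed across. The sentence before it awards points to categories. The two rules give the same value only when nobody eats more than one item from a category. Otherwise the item sum is larger, and it rises when a participant eats more variants of one staple without adding any food group, which is not what a diversity score should reward.

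The stated maximum of 12 and the bands that end at 12 suit a bounded count of categories. They do not suit an open count of foods. If an analyst or data manager coded the sentence as written, the values of a primary outcome and the input to its mixed model would be wrong, and some scores would have no band.

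**Working it through.** **Inputs.** All come from section 2.4.1.6: the two scoring sentences, the printed list of categories, the maximum of 12 and the three bands.

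**Step 1: try to reproduce the maximum of 12.** The middle column applies the 0/1 category rule. The last two columns apply the item rule. Count A takes the example foods in the three categories that have them, and one item for each other category. Count B takes every food word in the list.

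| Category | Category points | Items, count A | Items, count B |
|---|---|---|---|
| Cereals and grains | 1 | 6 | 6 |
| Roots and tubers | 1 | 1 | 2 |
| Eggs | 1 | 1 | 1 |
| Fish and shellfish | 1 | 1 | 2 |
| Legumes and nuts | 1 | 1 | 2 |
| Dairy | 1 | 3 | 3 |
| Fats and oils | 1 | 1 | 2 |
| Sugars and honey | 1 | 1 | 2 |
| Miscellaneous | 1 | 3 | 3 |
| **Maximum** | **9** | **18** | **23** |

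The cereals entry ends in an open-ended 'etc.', so 18 and 23 are lower limits for the largest item sum. Neither rule, applied to the printed list, gives 12.

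**Step 2: set the results against the bands.**

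- Category rule on the printed list: the range is 0 to 9. The high band (9 to 12) is reached only at exactly 9, that is, when all nine categories are eaten. Scores of 10, 11 and 12 cannot occur. The shortfall is 12 − 9 = 3 categories.
- Item rule: scores above 12 can occur and belong to no band.

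**Step 3: individual examples.**

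- The six named cereal foods and nothing else: 1 by category (low), 6 by item (medium).
- Bread, rice, noodles, biscuits, milk, cheese, beans, groundnuts, tea and a condiment: 4 categories (low), and 4 + 2 + 2 + 2 = 10 items (high). This record was chosen to show a large gap; it is not typical.

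**Step 4: illustration only, on assumed inputs.** The article gives no consumption data. Assume that each group is eaten independently with probability 0.6, and that an eaten group contributes 1 + Poisson(0.3) or 1 + Poisson(0.8) items, a mean of 1.3 or 1.8. Item scores above 12 are counted as high for the band comparison.

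| Groups | Items per eaten group | Mean by category | Mean by item | Change band | Item score above 12 |
|---|---|---|---|---|---|
| 9 | 1.3 | 9 × 0.6 = 5.4 | 5.4 × 1.3 = 7.0 | 37% | 1% |
| 9 | 1.8 | 5.4 | 5.4 × 1.8 = 9.7 | 79% | 20% |
| 12 | 1.3 | 12 × 0.6 = 7.2 | 7.2 × 1.3 = 9.4 | 42% | 12% |
| 12 | 1.8 | 7.2 | 7.2 × 1.8 = 13.0 | 69% | 53% |

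The percentages come from the exact joint distribution of the two scores under these assumptions. They show what would follow if the item sentence were coded literally. They say nothing about how likely that is. The direction needs no assumption: an item sum can never be lower than the category count.

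**The case against.** The strongest reply is that the section contains one operative rule. The score is described as resting on food groups, points are assigned to categories and nowhere to single foods, and a fixed maximum makes sense only for a bounded sum of 0/1 points. On that view, food items is loose wording for category points, and the clash with 12 is evidence that no item sum was meant. This is largely right. It rules out the stronger reading a reader might take from the two adjacent sentences, that a primary outcome has two competing definitions.

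It is also true that the bands are tied to a descriptive summary and that section 2.5 does not use them in the mixed model. The percentages in the illustration rest wholly on assumed inputs for a reading the authors probably did not intend.

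Two things survive. First, the sentence that defines the cumulative score is wrong as printed and gives wrong values to anyone who follows it. Second, the appeal to the maximum is weaker than it looks, because the category rule on the printed list gives 9. The stated 12 therefore cannot by itself confirm the category rule.

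A reader might also infer from the list that vegetables and fruits, the foods the intervention targets, will not be scored at all. As printed, the score could not register a change in their intake. But a maximum of 12 implies three categories beyond those shown, and the article may have abridged the questionnaire's list. The document does not establish that these groups will be left out of data collection, only that the list and the maximum disagree.

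**Conclusion.** The point holds as a wording error in the scoring rule of a primary outcome, together with a list that does not match its stated maximum. On the printed text the largest score is 9 by category and at least 18 by item, against 12 stated. These are direct counts and need no assumption beyond how the named foods are counted (18 or 23). The category count is taken as the intended rule; this is a judgement from the surrounding sentences, and a firm one. The shifts between bands are illustrative and should not be quoted as an expected effect on the trial. The correction is still worth making before analysis, because the score enters the mixed model and the error is easy to carry into code.

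**What to change.** In section 2.4.1.6:

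1. Replace the sentence on the cumulative score with: 'The DDS is the sum of the 0/1 category points; several items in one category count once.'
2. State that the low, medium and high bands apply to this category count.
3. Print every category that is scored, and make their number agree with the maximum and the top band. If the questionnaire has twelve categories, add the three that are missing from the list and say whether vegetables, fruits and meat are among them. If it has nine, the stated maximum and the 9–12 band must be revised.

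Items 1 and 2 cost two sentences and no new data. Item 3 costs a longer list if the questionnaire already holds twelve categories. If it holds only those printed, adding groups would mean changing the instrument, which must be settled before baseline collection so that both time points use the same list.
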